##### 40-week maintenance phase

Participants were encouraged to continue with their lifestyle prescriptions and sustain their behaviour change with the support of the Health*e*Steps app and the Hockey FIT Social Network. Men were encouraged to use the Network to share success stories, share resources (e.g., healthy recipes), ask questions and keep in touch with others in the group, including the Hockey FIT coach. The platform was a place where resources from the program were shared and made available to all participants. In addition to being used for casual exchange, the Hockey FIT Social Network platform was also used by the Head Coach to send out standardized messages (at 1, 3, 5, 6.5, 7.5 and 8.5 months following the active phase) containing reminders and encouraging messages about sustaining healthy lifestyle behaviours.

Six months after the completion of the Active Phase, participants were invited to attend a Hockey FIT Reunion (combining participants from both sites), which consisted of a one-hour booster session followed by lunch and free entry to a London Knights vs. Sarnia Sting game (held in London, ON). The Head Coaches from both London and Sarnia ran the booster session, which focused on reinforcing topics such as goal setting, stages of change and re-setting lifestyle prescriptions, and included an exercise segment focused on aerobic activities.

#### Outcome evaluation

At each site, all participants began the study at the same time and teams of research staff completed measurement sessions over an approximate 2-week period (at each time point). All randomized men were contacted at each follow-up, including those in the intervention group who did not complete the Hockey FIT program. Questionnaires were mailed for self-completion (and a time arranged with the study team for pick-up) for any participants who agreed to assessment but were not willing or able to come to a measurement session. Since the comparator group were offered the opportunity to take part in the Hockey FIT program shortly following the 12-week measurement session, individuals in this group did not participate in any follow up measurements beyond 12 weeks.

At baseline, participant demographic and clinical characteristics were collected including: age, marital status, education, occupation, ethnicity, health status, smoking status, medical conditions/history and medications.

##### Outcome measures

The following outcome measures were taken at baseline and 12 weeks in both groups, and then again at 12 months in the intervention group only:
*Objectively-measured clinical characteristics:* weight (kg and % of baseline weight), BMI (calculated from weight and height in kg/m^2^), waist circumference (cm), and resting systolic and diastolic blood pressure (BP; mmHg).
*Self-reported physical activity and sitting time:* average steps/day, measured using Yamax Digiwalker SW-200 pedometers and self-reported by participants using a 7-day paper log [57, 58]; total physical activity (Metabolic Equivalent (MET)-minutes/week) measured using the International Physical Activity Questionnaire (IPAQ) Short Form [59]; and time spent in sedentary activity (minutes spent sitting on a typical week day) measured with the IPAQ.
*Self-reported eating and alcohol:* healthful eating score, measured using Starting the Conversation (STC) questionnaire [60]; fatty food, and sugary food scores, as well as fruit and vegetable consumption, measured using a modified version of the Dietary Instrument for Nutrition Education (DINE) [61] and following scoring outlined by Hunt and colleagues [15]; and total alcohol consumption (units/week), measured using a 7-day recall diary [62].
*Psychological and health-related quality of life:* self-esteem score, measured using the Rosenberg Self-Esteem Scale (RSES); positive and negative affect scores, measured using the International Positive and Negative Affect Schedule Short Form (I-PANAS-SF) [63]; and self-rated health, using the European Quality of Life – 5 Dimensions – 3 Levels (EQ-5D-3 L) visual analog scale (VAS) score [64, 65].

All self-reported measures were collected using paper-based, self-administered questionnaires. Outcome measures were modelled after the FFIT evaluation but included a few differences: 1) the Hockey FIT evaluation replaced the Short Form-12 with the EQ-5D-3 L questionnaire for a simple measurement of health-related quality of life and pilot of the EQ-5D-3 L for ease of use for planning for a future economic evaluation; 2) Hockey FIT added the Starting the Conversation Questionnaire to obtain a simple single score of healthful eating; and 3) Hockey FIT also included measurement of physical activity via pedometers. See Table 2 for an overview of outcome measures and measurement protocols.

**Table 2 Tab2:** Overview of study outcomes and measurement details

Outcome	Equipment or instrument	Description
Objectively Measured Clinical Characteristics		
Weight (kg and % of baseline weight)	Digital weight scale (Tanita HD-351)	• Light clothing, no shoes and empty pockets • Blinded assessor post-baseline in private area
Body mass index (kg/m^2^)	Digital weight scale (Tanita HD‐351) Portable stadiometer (seca 213)	• BMI calculated using the participant’s objectively measured height and weight • Height measured without shoes
Waist circumference (cm)	Tape measure	• Follows protocol outlined by the Heart and Stroke Foundation of Canada • Two measurements taken to record an average; if measurements differ by more than 5 mm, a third measurement is taken and used in the average
Resting systolic blood pressure (BP) (mmHg)	Digital BP monitor (BP Tru BPM-100)	• Participants sit quietly for 5 min prior to the first measurement; 3 measurements will be taken, 2 min apart. The first one is discarded, and the average of the last two is recorded • Feet flat on the floor, arm free of clothing, cuff at the level of heart and arm resting, same arm used (left arm preferred), no talking
Resting diastolic BP (mmHg)		
Self-Reported Physical Activity		
Average steps/day	Pedometer (Yamax Digiwalker SW-200 with security strap)	• Participants wear pedometers during waking hours for a 7-day period (putting pedometer on upon waking and removing immediately before sleeping), but not during showering/ bathing • Participants are asked to wear the pedometer at the waist, centered over their most dominant foot • Participants record the number of steps completed each day on a paper-based tracking form
Total physical activity (MET-min/week^a^)	International Physical Activity Questionnaire (IPAQ) – Short Form	• Self-completed paper‐based questionnaire • Participants recall information on vigorous activities, moderate activities, walking, and sitting • Sedentary time is measured with a single question (minutes spent sitting on a typical week day) • The IPAQ provides guidelines for data processing and score creation
Time spent in sedentary activity (min/day)		
Self-Reported Eating and Alcohol		
Total healthful eating score	Starting the Conversation (STC)	• Self-completed paper-based questionnaire • Designed for dietary assessment and intervention in a clinical setting • Participants recall eating habits over the past few months (on average) on 8 different items • A total healthful eating score (possible range 0–16) is calculated, whereby a lower score indicates a more healthful diet
Fatty food score	Modified version of the Dietary Instrument for Nutrition Education (DINE)	• Self-completed paper-based questionnaire • Participants recall eating habits over the last 7 days • Fruit and vegetable consumption is measured with a single question • Methods published by FFIT will be followed to calculate a fatty food score (possible range 8–68) and sugary food score (possible range 3–16), with higher scores indicative of higher consumption
Sugary food score		
Sugary food score		
Total alcohol Consumption (units/week)	7-day recall diary	• Self-completed paper-based diary • Participants recall alcohol consumption (beer, cider/cooler, wine, distilled alcohol, and other) over the last 7 days • Total alcohol consumption is calculated by summing the number of drinks across the categories for each day and then summing the total number of drinks/day
Psychological and Health-Related Quality of Life		
Self-esteem score	Rosenberg Self Esteem Scale (RSES)	• Self-completed paper-based questionnaire • Consists of 10 items assessing global self- esteem; 5 items have positively worded statements and 5 are negatively worded • Participants are asked to reflect on their current feelings (i.e., the extent to which they agree or disagree with each statement) • A summary score (possible range 0‐30) is calculated to provide a measure of self-esteem, where higher scores indicate higher self- esteem
Positive Affect Score	International Positive and Negative Affect Schedule Short Form (I‐PANAS‐SF)	• Self-completed paper-based questionnaire • Consists of 10 words that describe different feelings or emotions (half positive, half negative) • Participants rate how they normally feel, from 1 = never to 5 = always • Positive and negative affect sub‐scale scores are calculated (both range 5‐25), where higher scores indicate higher levels of positive affect, and negative affect, respectively
Negative Affect Score		
Self-Rated Health [visual analog scale (VAS) score]	European Quality of Life 5 Dimensions Questionnaire - 3 Level Version (EQ‐5D- 3 L)	• Self-completed paper-based questionnaire • For purposes of this study, the VAS score will be used to assess current state of health on a scale from 0 (worst imaginable state of health) to 100 (best imaginable state of health)

^a^METs (metabolic equivalents) are multiples of the resting metabolic rate; *MET-minute* multiplying the MET score of an activity by the minutes performed

#### Participant appreciation

All participants received free promotional materials from GoodLife and Sarnia Sting/London Knights hockey teams (e.g., bags, t-shirts). Participants also received a Hockey FIT t-shirt, a Hockey FIT puck, a healthy lunch and free game tickets if they attended the reunion/booster session. Further, the intervention group received a $20 gift card to a local sports store if they attended the 12-month measurement session. Attendance raffles were held at the end of the 12-week active phase to encourage attendance at all 12 sessions (i.e., participants received one ticket for each session they attended). See Table 3 for an overview of participant appreciation.

**Table 3 Tab3:** Participant appreciation in the Hockey FIT pilot study

Time point	Description
During program sessions	• GoodLife Fitness water bottles • GoodLife Fitness duffle bags • Hockey team t-shirt or track jacket
Attendance raffle	• Signed hockey jerseys • Signed hockey sticks • Cookbook • Water bottles • Gift cards • Baseball caps • Cereal • Umbrella
9-month reunion & booster session	• Hockey FIT t-shirts • Hockey FIT pucks • Gift bags from sponsor (Bank of Montreal) • Healthy lunch • Hockey game ticket (London Knights vs. Sarnia Sting)
12-month measurement session (Intervention Group)	• $20 gift cards to a local sports store

#### Statistical analysis for outcome evaluation

For all outcome measures, observed values at baseline and 12 weeks will be summarized descriptively for each group. In addition, for the Hockey FIT group only, observed values at 12 months will be summarized descriptively. For data (average steps/day), participants were required to have at least three complete days of data, in order for data to be utilized in analyses [66].

Analyses will be performed following intent-to-treat principles; thus, we will include all participants with at least valid baseline data according to the randomization scheme and regardless of compliance with the intervention and data at follow-up. We will analyze data using mixed models for repeated measurements; linear mixed models will be used for continuous outcomes and generalized linear mixed models will be used for categorical and discrete outcomes. We will follow recommendations of Fitzmaurice et al. [67] and retain the baseline outcome as part of the outcome vector and constrain the group means as equal because of randomization. For all models, we will examine differences between groups at 12 weeks and changes within groups from baseline to 12 weeks (and to 12 months for the intervention group).

Terms included in models will include time, group (treatment) × time, age and site. Time will be modeled categorically with indicator variables (with baseline as the reference category). Residuals from models will be examined and subject to assumptions checks.

Based on our past experience, we do not expect substantial missing data; nonetheless, results will be valid provided data are missing at random and no imputation of data will be required by using a mixed model analysis approach [67]. To address participant dropout, we will also compare baseline characteristics of men who dropped out versus men who were included in the analysis. Interpretation of study results will primarily be based on estimation and associated 95 % confidence intervals. Two-sided *p*-values less than 0.05 will be reported as statistically significant. Analyses will be performed using SAS version 9.4 (SAS Statistical Analysis Software).

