#### Recruitment & participants

Participants were recruited through a variety of methods: team email blasts, team social media accounts (i.e., team twitter feed posts), posters, traditional media-based advertisements (newspaper, TV, radio, community magazines), Hockey FIT website [51], word of mouth, and/or direct contact with potential recruits at the OHL team arena on game day. Those interested in participating in the study contacted the Hockey FIT Research Coordinator by email or telephone. The Research Coordinator pre-screened individuals for eligibility by phone or email; specifically, interested individuals were asked about their gender, age, height, weight and availability to attend Hockey FIT sessions on a certain day of the week, for 12 weeks, starting on a set date. Individuals deemed likely to be eligible were then invited to attend an in-person screening session. *Inclusion criteria:* Men aged 35–65 years, with an objectively measured BMI of at least 28 kg/m^2^, and meet safety requirements using the Physical Activity Readiness Questionnaire (PAR-Q) [52]. *Exclusion criteria:* Unable to comprehend the letter of information and consent documentation.

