#### Randomization, allocation & blinding

Following baseline measurement (including seven days of tracking steps via a pedometer), participants returned for an enrolment and allocation session. The randomization sequence was computer-generated [1:1 in block sizes of 4 and stratified by site (London or Sarnia), using SAS version 9.4 (SAS Statistical Analysis Software)] and concealed using opaque envelopes until interventions were assigned (by an individual not involved in generating the randomization sequence). Participants were allocated in correspondence to the numerical order of the randomization envelopes and their order of appointments.

All participants (intervention and comparator) were provided with copies of Canada’s Food Guide [48] and the Canadian Physical Activity Guidelines [49]. All participants were also given an adverse events log and the research team member allocating participants stressed the importance of keeping the research team and/or their Hockey FIT coach informed of any injuries, illnesses, or changes in medication for the entirety of the study. Participants allocated to the intervention group were informed to keep their pedometer for use over the duration of the program. Participants allocated to the comparator group were asked to return their pedometer and continue with usual activities, without further intervention from the research team. Following completion of the 12-week measurement sessions, participants in the comparator group were invited to take part in the Hockey FIT program, following the exact same protocol as the intervention group.

Due to the nature of the study, participants and coaches could not be blinded to group allocation. During 12-week measurement sessions, a blinded assessor conducted all weight measurements in a separate room; no other measurements were blinded.

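### The analysis set requires valid baseline data, which the chosen constrained-baseline mixed model does not need; the rule could drop men with usable 12-week values, mainly for steps/day, at a small cost in precision

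*Protocol article*

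**What the plan says.** All of the rule stands in the protocol article, under Statistical analysis for outcome evaluation.

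- Principle: "Analyses will be performed following intent-to-treat principles".
- Analysis set: "we will include all participants with at least valid baseline data according to the randomization scheme", and then "regardless of compliance with the intervention and data at follow-up".
- Model: the analysts will "retain the baseline outcome as part of the outcome vector and constrain the group means as equal because of randomization". The fixed terms are time, group by time, age and site.
- Missing data: "results will be valid provided data are missing at random and no imputation of data will be required".
- Validity of step counts: "participants were required to have at least three complete days of data, in order for data to be utilized in analyses".

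Two earlier sections bear on how often the rule could matter. Randomization, allocation & blinding gives the order of events: "Following baseline measurement (including seven days of tracking steps via a pedometer), participants returned for an enrolment and allocation session". Recruitment & participants makes entry conditional on men "with an objectively measured BMI of at least 28 kg/m^2", so weight and height were measured before allocation in every eligible man.

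**The concern.** The analysis set and the model do not match. A baseline value is indispensable when baseline enters as a covariate, because a man without it then has no complete row. Here baseline is part of the outcome vector. A man with only a 12-week value has an incomplete vector, exactly as a man with only a baseline value has, and the likelihood uses both. Yet the rule admits the second man and shuts out the first, who is the one with direct information on the 12-week group difference.

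The wording also does not say whether valid baseline data is judged separately for each outcome or once for the man. On the first reading, a man with a poor baseline pedometer week is lost to the steps/day analysis even if his 12-week log is complete. On the second, the same poor week could remove him from other outcomes too.

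At stake are the precision of the 12-week contrast in a trial of 80 men that is to be read mainly through 95% confidence intervals, and whether the analysed set matches the intent-to-treat label.

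**Working it through.** **The plan's own figure.** The article gives no figure for this point. Its only calculation is the size of the later full-scale trial (difference 5%, SD 19.9%, 80% power, two-sided 0.05). The normal formula gives 249 per arm and the t-test version 250, as stated. Allowing 25% loss gives 250/0.75 = 333.3, so 334 against the stated 335. Neither number depends on the analysis set rule.

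**Can the model use a man without baseline?** Yes. His 12-week value has mean and variance defined by the model. His age, site and arm are known, since age is an entry criterion and site is the randomization stratum.

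**What does exclusion cost?**

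Inputs from the article: 80 men, so 40 per arm; baseline mean common to both arms.

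Assumed, because the article does not give them: *m* men per arm have a valid 12-week value but no valid baseline value; the other 40 − *m* have both; equal variances (set to 1); ρ is the baseline to 12-week correlation; covariance treated as known; age and site ignored.

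With the baseline difference fixed at zero, each man with both values contributes 1/(1 − ρ²) to his arm's information on the 12-week difference. A man with only the 12-week value contributes 1. Hence

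- excluded: Var = 2(1 − ρ²)/(40 − *m*)
- retained: Var = 2 / [(40 − *m*)/(1 − ρ²) + *m*]
- ratio, excluded to retained: 1 + *m*(1 − ρ²)/(40 − *m*)

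Example, *m* = 4 and ρ = 0.5: excluded 2 × 0.75/36 = 0.0417 (SE 0.2041); retained 2/(36/0.75 + 4) = 2/52 = 0.0385 (SE 0.1961); ratio 1 + 4 × 0.75/36 = 1.083.

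Increase in variance from exclusion:

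| Men of 80 (*m* per arm) | ρ = 0.5 | ρ = 0.7 | ρ = 0.9 |
|---|---|---|---|
| 2 (1) | 0.75/39 = 1.9% | 0.51/39 = 1.3% | 0.19/39 = 0.5% |
| 4 (2) | 1.50/38 = 3.9% | 1.02/38 = 2.7% | 0.38/38 = 1.0% |
| 8 (4) | 3.00/36 = 8.3% | 2.04/36 = 5.7% | 0.76/36 = 2.1% |

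For ρ between 0.5 and 0.7 the range is about 1% to 8% in variance. The standard error, and so the width of the confidence interval, rises by about 0.7% (√1.013) to 4.1% (√1.083). With *m* = 0, as expected for weight and BMI when the rule is read per outcome, the increase is zero.

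**The case against.** The strongest reply is that the sentence is there to include, not to exclude. It goes on to keep men "regardless of compliance with the intervention and data at follow-up", so its main purpose is to hold non-compliers and men without follow-up in the analysis. Allocation followed the baseline session, so attending baseline was the route to randomization. If the phrase describes the man and means only that he was measured at baseline, the set may be everyone randomized. This stands as far as it goes: the article identifies no randomized man without valid baseline data. It does not remove the point, because the condition is written and its scope is not defined.

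Three stronger readings are tempting, and the article does not support them.

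- *That randomized men are being discarded.* The text shows only that they could be.
- *That the group comparison is biased.* The baseline data were collected before allocation, so whether they are valid cannot depend on the arm. The comparison among the men retained is still a randomized one.
- *That the loss is large or widespread.* With 16 of 80 men affected, the formula would give 12.8% to 18.8% more variance (8 × 0.51/32 to 8 × 0.75/32). But the plan expects little missing data, and for steps/day a man would have to miss the three-day threshold at baseline and then meet it at 12 weeks. Steps/day is also the only outcome with an explicit validity rule. The article does not say that a questionnaire score with missing items is invalid, and such rules commonly belong in a fuller document that is not shown.

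**Conclusion.** The point holds as a minor one. The baseline condition is not needed by the model, is narrower than the intent-to-treat principle it is said to follow from, and is unclear on whether it applies per outcome or per man. Its likely reach is steps/day. Only on the across-all-measures reading could it touch other outcomes, weight included.

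The size is conditional. The number of men affected and the correlation are assumptions, and so is the premise that every affected man has a 12-week value. Within the range shown, the loss is small. No sample size and no confirmatory test depends on it, since this is a pilot. It is worth correcting because the correction gains precision for nothing and because the same analysis plan may be carried into the intended full-scale trial.

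**What to change.** Replace the analysis set sentence with: for each outcome, all randomized men with at least one valid measurement of that outcome, at baseline or follow-up, will be analysed in the arm to which they were randomized, regardless of compliance.

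This still keeps men who have only a baseline value, admits those who have only a follow-up value, and settles that validity is judged outcome by outcome. The three-day rule for step counts can stay as it is, applied to each measurement week separately.

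The cost is one sentence. The model, the data collected and the sample size do not change. The change should be made before the outcome data are analysed.

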#### Sample size

A recruitment target of 80 male hockey fans of the London Knights and Sarnia Sting (40 per team; 20 men per arm within each team) was based on a sample size calculation for a subsequent full-scale RCT, following methods by FFIT [15]. To detect a 5 % difference in weight loss between intervention and comparison groups at 12 months, with a standard deviation of 19.9 %, 80 % power and a 0.05 two-sided significance level, 250 men are required in each arm [50]. To allow for 25 % loss to follow-up, a very conservative estimate, the sample size was increased to 335 men in each arm. A target of 670 men reflects the need to recruit 40 male hockey fans from 17 different OHL teams. The need to recruit 40 male hockey fans per site is reflected in this pilot trial.

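### Weight as a percentage of baseline does not fit the stated mixed model, because with baseline kept as a response every man's first value is exactly 100 %

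*Protocol article*

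**What the plan says.** Under Outcome measures, the first objectively measured outcome is "weight (kg and % of baseline weight"; Table 2 repeats both forms. The list is introduced with "The following outcome measures were taken at baseline and 12 weeks in both groups", and the intervention group is measured again at 12 months.

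The section Statistical analysis for outcome evaluation states that "linear mixed models will be used for continuous outcomes". The baseline is handled as follows: the team will "retain the baseline outcome as part of the outcome vector and constrain the group means as equal because of randomization". Time is categorical, with baseline as the reference. On the model terms: "Terms included in models will include time, group (treatment) × time, age and site". On scope: "For all models, we will examine differences between groups at 12 weeks and changes within groups from baseline to 12 weeks". On the analysis set: "we will include all participants with at least valid baseline data according to the randomization scheme".

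No exception is made for the percentage form of weight, no other response is named for it, and no covariance structure is given. The section also says that model residuals will be checked and that interpretation will rest mainly on estimates with 95 % confidence intervals.

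**The concern.** A model with baseline in the response vector and a common baseline mean is a good choice for an outcome that varies between men at baseline. It borrows strength from the correlation between baseline and follow-up, and it keeps men who have a baseline value only.

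Percentage of baseline weight has neither property. Its baseline value is 100 for every man (or 0, if expressed as change). The common-mean constraint is met trivially and there is no correlation to borrow. A man with baseline data only contributes a constant. The covariance model must also describe a visit with zero variance alongside one with real variance.

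At stake are the standard error, confidence interval and p-value of the 12-week difference in percentage weight. Weight loss comes first among the health outcomes in Aim 2, and the article says a large trial will follow if the pilot looks promising. An interval that is too narrow would lean towards that reading.

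**Working it through.** **The plan's own figure.** The only calculation in the article is the full-scale sample size, framed as a 5 % "difference in weight loss between intervention and comparison groups at 12 months" with SD 19.9 %, two-sided alpha 0.05 and 80 % power.

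- n per arm = 2 × (1.960 + 0.842)² × 19.9² / 5² ≈ 249 (normal approximation), or 250 (t-based). The article states 250.
- 250 / 0.75 = 333.3, so 334. The article states 335.
- 670 / 40 = 16.75, so 17 teams, as stated.

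The figure reproduces to within rounding and is not in dispute.

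**Inputs for the check.** From the article: 80 men, 40 per arm, baseline and 12 weeks in both arms, 12 months in the intervention arm only, and the model terms above. Assumed: a 12-week SD of 4 percentage points and, where 12 months is included, a correlation between 12 weeks and 12 months (0.7 in the runs that state it). The article gives neither. Write s² for the 12-week variance.

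**Case 1: unstructured covariance.** Var(baseline) = 0 and Cov(baseline, 12 weeks) = 0, so the matrix is singular. As the fitted baseline SD shrinks, the log-likelihood for 80 men rises by 80 × ln(1/SD):

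| Baseline SD | Log-likelihood kernel |
|---|---|
| 1 | −105 |
| 0.01 | −105 + 80 × ln(100) = −105 + 368 = 263 |
| 0.000001 | −105 + 80 × ln(1,000,000) = −105 + 1105 = 1000 |

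There is no maximum. The same holds for any structure with a separate variance at each visit.

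**Case 2: constant variance over time (random intercept or compound symmetry).** With two visits the model estimates one variance, (0 + s²)/2 = s²/2, and a covariance of 0.

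- Difference between groups at 12 weeks: model variance (s²/2)(1/40 + 1/40); true variance s²(1/40 + 1/40). SE ratio = 1/√2 = 0.707.
- The nominal 5 % test therefore rejects when |Z| > 1.960 × 0.707 = 1.386, which has probability 16.6 %. A nominal 95 % interval covers about 83 %.
- Change within a group: model variance (s²/2)(1/40 + 1/80) = 3s²/160; true variance s²/40 = 4s²/160. SE ratio = √0.75 = 0.87. The test rejects when |Z| > 1.697, about 9 %.

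The ratios do not depend on s. They do depend on the constant-variance assumption.

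**Simulation of case 2.** No true effect, 40 men per arm, several independent sets of 200 to 400 runs:

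| Setting | Model SE / true SE | Rejection at nominal 5 % |
|---|---|---|
| Two visits | 0.67 to 0.72 | 14 to 20 % |
| With 12 months in the intervention arm | 0.71 to 0.77 | 14 to 18.5 % |
| Baseline removed from the response; 12-week percentage weight on group, age and site | 0.90 / 0.91 = 0.99 | 5.7 % |

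The spread is mostly simulation error: at 16.6 % and 300 runs, the standard error is √(0.166 × 0.834 / 300) = 2.1 percentage points. One set also examined the within-group change and found 9.7 %, against about 9 % from the algebra.

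**The case against.** The strongest reply is that the numerical harm depends on a choice the article does not make. Unstructured covariance is common with categorical time. It would fail in plain sight and force another approach, so no falsely narrow interval would be reported. Covariance structure is also a detail that an article may leave to an analysis plan that is not shown. This stands. A reader might infer that the confidence interval will be too narrow; the article supports only that it would be under a constant-variance structure.

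Second, residual checks are planned, and a constant-variance fit would show almost no spread at baseline and full spread at 12 weeks. This also stands as a partial safeguard, although the article does not say what would then be done.

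Third, the percentage may simply be another expression of weight, derived from the kg model. That would be sound and the text does not forbid it. But the text does not say so either. It lists the percentage as an outcome and then states a rule for all models, and that rule as written does not suit it. This is a stated rule that misfits a listed outcome, so it is more than an omitted detail.

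Fourth, a reader might infer that the pilot's weight result as a whole, or the full-scale sample size, is undermined. The documents do not support either. Weight in kg has a genuine baseline and suits the model. The sample size is already computed, concerns 12 months, and is not said to be revised from the pilot's 12-week interval. No primary outcome or go/no-go rule is tied to this analysis.

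**Conclusion.** The point holds in limited form. As written, the model cannot validly analyse weight as a percentage of baseline. Either it has no likelihood maximum, or it runs with a 12-week between-group SE about 0.7 of the true value and a test at roughly 14 to 20 % instead of 5 %. The first outcome needs no assumption beyond visit-specific variances. The second rests on a constant-variance structure that the article does not specify and on the residual check not leading to a correction.

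The fault lies in the precision; no bias in the 12-week point estimate has been shown. It would be too strong to say that percentage weight cannot be analysed at all, since simple valid analyses exist. The point touches one of two expressions of one outcome in an exploratory pilot. That makes it moderate: worth correcting before the analysis is run, but no threat to the trial's other results.

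**What to change.** Add one sentence to the statistical analysis section exempting percentage weight from the general rule, with one of these analyses:

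- **Log weight.** Fit the same constrained-baseline model to log(weight) and back-transform. If d is the 12-week group contrast, 100 × (exp(d) − 1) is the percentage difference in weight. The within-group changes at 12 weeks and 12 months back-transform in the same way. This keeps a genuine baseline value and every man with baseline data.
- **ANCOVA.** Regress 12-week percentage change on arm, baseline weight (kg), age and site. This is simpler, but it uses only men weighed at 12 weeks and does not by itself give the within-group changes.

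Either is valid; the log model stays closer to the rest of the plan. Keep the stated model for weight in kg and for every outcome with a genuine baseline value. The cost is one sentence and a few lines of SAS code, with no new data.
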